### Statistical Analyses

#### General Approach

Checks of assumptions underlying statistical procedures will be performed and all corrective procedures will be applied as necessary. All analyses will involve 2-sided hypothesis tests, with α=.05 and adjusted for any multiple comparisons within the family of tests as appropriate.

Group equivalence will be assessed through univariate tests of association between treatment groups (EaseVRx/Sham VR) for all baseline demographic and clinical variables with chi-square and Kruskal–Wallis tests applied as appropriate. If statistically significant differences between groups are found for any variables (*P*<.05), those will be controlled for in the mixed models.

The data will be analyzed in a mixed-model framework (PROC GLIMMIX in SAS) with 3 explanatory factors: treatment group, time, and time × treatment group. Treatment group, EaseVRx versus Sham VR, will be specified as a between-subjects factor. Time will be specified as a within-subjects factor. The effect of interest will be the time × treatment group effect which tests whether the treatment group influenced the trajectory of the key variables over time.

The analytic method used will not involve imputing missing data for estimating the significance of the effects specified in the model. However, the predicted values from the estimated model will be used for reporting the findings. Given the safety of this treatment, there is no plan to conduct interim analyses.

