#### Secondary Analyses

Several analyses will be proposed.

First, we will compare the PGIC scale at end of treatment and follow-ups.

Second, we will repeat similar analyses as above for 2 time points, baseline and immediately following the 8-week intervention for opioid drug use, PROMIS physical function, PROMIS sleep disturbance, PSEQ-2, PCS, and CPAQ-8.

Finally, we will repeat similar analyses as above for 2 time points, the day immediately following the 8-week intervention and 1 month after the intervention for DVPRS Pain Rating, opioid drug use, PROMIS physical function, PROMIS sleep disturbance, PSEQ-2, PCS, and CPAQ-8.

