#### Exploratory Analyses

A number of exploratory analyses will be conducted, all of which envisage the above linear mixed modeling strategy with time points and variables as specified below.

First, we will assess Intervention × Time effects for a number of health-related outcome metrics (eg, number of steroid injections, emergency department visits, hospital admissions) at 2 time points, Day 9 and immediately following the 8-week intervention.

Second, we will repeat the above analyses for the period comprising the end of the 8-week intervention and at 3 and 6 months after the intervention.

Third, we will assess Intervention × Time effects for DVPRS Pain Rating, opioid drug use, PROMIS physical function, PROMIS sleep disturbance, PSEQ-2, PCS, CPAQ-8, Patient satisfaction, and PANAS for the periods comprising the 8-week intervention and at 1, 2, 3, and 6 months after the intervention. We will use a 2-factor ANOVA with intervention (EaseVRx vs Sham VR) as an independent groups factor and time as a dependent groups factor. Two-sided post hoc *t*-tests (adjusted for multiple comparisons) will be utilized to isolate the locus of any effects.

Fourth, we will examine the time course of changes in pain skills (eg, controlled breathing, meditation) from baseline, at the end of the 8-week intervention, and at 1, 2, 3, and 6 months after the intervention only in the EaseVRx group. We will use a one-factor repeated-measures ANOVA. Two-sided post hoc *t*-tests (adjusted for multiple comparisons) will be utilized to isolate the locus of any effects. When appropriate, we will also utilize more robust statistical approaches that better address missing data and do not assume distributional normality, such as bootstrapping.

In subsequent manuscripts, we will explore potential covariants of treatment response and possible mechanisms of actions.

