### Conclusions

This study will be one of the most rigorous in assessing the impact of self-administered VR therapy in community-based individuals with chronic lower back pain and the first to use a placebo VR therapy program. Its remote design will allow it to be completed during a global pandemic in a pragmatic and nationally representative sample. This will also be the first study to assess VR therapy’s durability for chronic pain over a 6-month posttreatment follow-up period. Results from this study will provide critical data on how individuals with chronic lower back pain may use self-administered VR therapy at home for symptom management and functional improvement.

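### The secondary 1-month analysis leaves out the pre-treatment baseline, so its designated test can detect loss of benefit but cannot show benefit over Sham VR at month 1

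*Protocol article*

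**What the plan says.** - **Secondary Analyses, last item.** The model is refitted "for 2 time points, the day immediately following the 8-week intervention and 1 month after the intervention for DVPRS Pain Rating" and for opioid use, the two PROMIS scales, PSEQ-2, PCS and CPAQ-8. The item opens "Finally, we will repeat similar analyses as above for 2 time points", so it takes over the model already described.
- **General Approach.** This fixes what that model tests: "The effect of interest will be the time × treatment group effect which tests whether the treatment group influenced the trajectory of the key variables over" (…).
- **Secondary Analyses, second item.** The end-of-treatment analysis is run "for 2 time points, baseline and immediately following the 8-week intervention for opioid drug use, PROMIS physical function" and other measures. Baseline is named where it is used.
- **Introduction, Protocol Overview and Conclusions.** The Introduction hypothesizes benefit over the control during treatment and follow-up. Protocol Overview says durability will be tested at months 1, 2, 3 and 6. Conclusions presents the trial as the first to assess "durability for chronic pain over a 6-month posttreatment follow-up period".
- **Exploratory Analyses.** The section introduces its analyses as ones "all of which envisage the above linear mixed modeling strategy". Its third item covers DVPRS and other outcomes over the treatment period and months 1, 2, 3 and 6, and then states: "We will use a 2-factor ANOVA with intervention (EaseVRx vs Sham VR) as an independent groups factor".

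The article gives no maintenance margin and no rule for reading a non-significant 1-month interaction.

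**The concern.** The follow-up question is whether participants given EaseVRx are still better off than those given Sham VR some time after treatment stops. The designated 1-month test addresses a neighbouring question: does the gap between arms widen or narrow between end of treatment and month 1? A treatment whose benefit lasts in full and a treatment that never worked give the same expected answer.

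At stake is the one secondary-tier result on pain after treatment. If the benefit persists, the expected result is non-significant and gives no support for the stated hypothesis. With no rule for interpreting a null result, there is also a risk that it is taken as maintenance.

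A smaller matter lies in Exploratory Analyses. The section promises the linear mixed model throughout and then names a 2-factor ANOVA for the longer follow-up. A conventional repeated-measures ANOVA would usually drop participants with a missed visit, whereas the mixed model would keep them.

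**Working it through.** **1. What the interaction estimates.** Let B1 be the EaseVRx-minus-Sham benefit (extra pain reduction) at end of treatment and B2 the benefit at month 1. Randomization makes the expected baseline difference zero.

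- Planned interaction (end of treatment, month 1): B2 − B1.
- Baseline-referenced interaction (baseline, month 1): B2 − 0 = B2.

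If B1 = B2 = 0.724, the planned term is 0. If B1 = B2 = 0, it is also 0. This step needs no numerical assumption and carries the finding.

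**2. The plan's own figures (Sample Size Determination).**

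- Effect: 1.48 − 0.756 = 0.724 points.
- Attrition: 45 / (1 − 0.40) = 75 per group, which reproduces the stated figure.
- The 45 per group cannot be reproduced independently, because no SD or correlation is given. Solving n = 2·SD²·(1.960 + 1.282)² / 0.724² for SD at n = 45, two-sided α = .05 and 90% power gives SD = 0.724 / (√(2/45) × 3.242) ≈ 1.06.

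**3. Illustration.** Assume that this SD of change applies to both contrasts, with 45 completers per arm. Then SE = 1.06 × √(2/45) ≈ 0.223. The probability of P<.05 is Φ(δ/SE − 1.96) + Φ(−δ/SE − 1.96), where δ is the expected contrast.

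| Situation at month 1 | δ planned (absolute) | Planned test | δ from baseline | Baseline-referenced test |
|---|---|---|---|---|
| Benefit fully kept | 0 | 5% | 0.724 | 90% |
| 75% kept | 0.181 | 13% | 0.543 | 68% |
| Half kept | 0.362 | 37% | 0.362 | 37% |
| All lost | 0.724 | 90% | 0 | 5% |
| Never any benefit | 0 | 5% | 0 | 5% |

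The first and last rows are identical for the planned test and differ for the baseline-referenced one.

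**4. Sensitivity to the SD (benefit fully kept, 45 per arm).** At an assumed SD of 1.5, the planned test is significant 5% of the time and the baseline-referenced test about 63%. At SD 2.0 the figures are 5% and about 40%.

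**5. Why a null would not establish maintenance.** The 95% CI half-width is 1.96 × 0.223 ≈ 0.44 points at 45 per arm. A planned contrast estimated at exactly zero would not exclude loss of half the benefit (0.362). If half really is lost, the planned test misses it about 63% of the time at 45 per arm, 45% at 75 and 37% at 90.

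**The case against.** Several points on the other side are sound.

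- **The month-1 difference is recoverable.** General Approach says that model-predicted values will be used for reporting, and these include arm means at month 1. Under 1:1 randomization their difference is a valid treatment effect even without baseline. A reader might infer that the month-1 benefit cannot be estimated at all, and the article does not support that. What stands is that the article designates the interaction, not this difference, as the effect of interest.
- **The test does bear on durability.** It is two-sided and can detect loss of benefit. End of treatment enters as an outcome in a within-subject contrast between randomized arms, so the choice of reference does not bias the comparison. It answers a different question.
- **Other analyses cover follow-up.** PGIC is compared at the follow-ups in the secondary tier, and the third exploratory item could give arm contrasts by visit through its post hoc tests. These soften the gap without closing it. PGIC is a global rating and not a pain score. The exploratory item is lower tier and does not clearly include the pre-treatment baseline.
- **The objectives rank follow-up effects over 6 months as exploratory.** That limits the weight of the point. The 1-month analysis nevertheless sits under Secondary Analyses.
- **The 37% power to detect loss of half the benefit is not caused by the reference.** The baseline-referenced test has the same 37% when half remains. That figure reflects sample size, and the 45 per arm assumes that the 40% attrition contingency occurs.

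Three further readings go beyond the text. One is that a null result will be reported as durability; nothing says so, and it is only a risk left open by the missing rule. Another is that the exploratory ANOVA is restricted to completers; no such restriction is stated, and the section allows approaches that handle missing data better when appropriate. The third is that the exploratory item beginning "we will repeat the above analyses for the period comprising the end of the 8-week intervention and at 3 and 6 months" repeats the defect for pain; it directly follows the health care use analysis and most naturally refers to those outcomes.

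**Conclusion.** The point holds in this form: the designated secondary test at 1 month has expectation zero both under full persistence and under no effect at any time. It therefore cannot support the hypothesis of benefit through follow-up or the durability aim, although it can reveal decay. This follows from the two named visits and the named effect of interest.

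Brevity does not explain the omission, since the preceding item in the same section names baseline and this one names a different reference.

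The size (5% against about 90% for a fully kept benefit, or 63% and 40% at SDs of 1.5 and 2.0) is an illustration. It rests on a back-solved SD from a 21-day study, carried to both contrasts, at 45 per arm. The conflict between the ANOVA and the mixed-model statement in Exploratory Analyses is real but secondary. The primary analysis is unaffected.

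**What to change.** 1. In Secondary Analyses, fit the mixed model with pre-treatment baseline, end of treatment and the follow-up visits. Designate the EaseVRx-minus-Sham difference in change from baseline at month 1, with its 95% CI, as the secondary estimate. Report months 2, 3 and 6 in the same way as exploratory.
2. Keep the end-of-treatment-to-month-1 contrast as a description of decay, and state that a non-significant result is not evidence of maintenance. If maintenance is to be claimed, set a margin in advance and judge the CI against it.
3. In Exploratory Analyses, replace the 2-factor ANOVA with the linear mixed model that the section says it uses.

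The cost is wording only. Table 2 already schedules baseline, end of treatment and month 1 for all seven measures in the 1-month analysis.

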#### Exploratory Analyses

A number of exploratory analyses will be conducted, all of which envisage the above linear mixed modeling strategy with time points and variables as specified below.

First, we will assess Intervention × Time effects for a number of health-related outcome metrics (eg, number of steroid injections, emergency department visits, hospital admissions) at 2 time points, Day 9 and immediately following the 8-week intervention.

Second, we will repeat the above analyses for the period comprising the end of the 8-week intervention and at 3 and 6 months after the intervention.

Third, we will assess Intervention × Time effects for DVPRS Pain Rating, opioid drug use, PROMIS physical function, PROMIS sleep disturbance, PSEQ-2, PCS, CPAQ-8, Patient satisfaction, and PANAS for the periods comprising the 8-week intervention and at 1, 2, 3, and 6 months after the intervention. We will use a 2-factor ANOVA with intervention (EaseVRx vs Sham VR) as an independent groups factor and time as a dependent groups factor. Two-sided post hoc *t*-tests (adjusted for multiple comparisons) will be utilized to isolate the locus of any effects.

Fourth, we will examine the time course of changes in pain skills (eg, controlled breathing, meditation) from baseline, at the end of the 8-week intervention, and at 1, 2, 3, and 6 months after the intervention only in the EaseVRx group. We will use a one-factor repeated-measures ANOVA. Two-sided post hoc *t*-tests (adjusted for multiple comparisons) will be utilized to isolate the locus of any effects. When appropriate, we will also utilize more robust statistical approaches that better address missing data and do not assume distributional normality, such as bootstrapping.

In subsequent manuscripts, we will explore potential covariants of treatment response and possible mechanisms of actions.

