**Methods:**

We will randomize 180 individuals with cLBP to 1 of 2 VR programs: (1) EaseVRx (8-week skills-based VR program); or (2) Sham VR (control condition). All participants will receive a VR headset to minimize any biases related to the technology’s novelty. The Sham VR group had 2D neutral content in a 3D theater-like environment. Our primary outcome is average pain intensity and pain-related interference with activity, stress, mood, and sleep. Our secondary outcomes include patient-reported physical function, sleep disturbance, pain self-efficacy, pain catastrophizing, pain acceptance, health utilization, medication use, and user satisfaction. We hypothesize superiority for the skills-based VR program in all of these measures compared to the control condition. Team statisticians blinded to treatment assignment will assess outcomes up to 6 months posttreatment using an approach suitable for the longitudinal nature of the data.

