#### Additional Custom Surveys

Several custom surveys were developed for the study, including one designed to assess satisfaction with each condition. Another assesses device usability, enjoyment or difficulties, and the likelihood to continue treatment. Additional items will assess pain knowledge and pain management skills use (eg, use of relaxation and controlled breathing during the previous 7 days). We will also assess patient perception of the study arm using a single item administered to both groups in the 6-month follow-up survey.

**Table 1 table1:** Variable/category, measure name, rank, and number of items for all measures.

Variable or Category		Measure	Number of items or units

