**Secondary Outcomes**			
	Global impression of change	Patient’s Global Impression of Change (PGIC) [38]	1
	Physical function	PROMIS^b^ Physical Function [40]	6
	Sleep disturbance	PROMIS Sleep Disturbance [41]	6
	Acceptability	Custom Patient Satisfaction	8 + 15 open-ended questions
	Adherence	Custom Device Utilization survey	1
	Adherence	VR^c^ usage data	Seconds/week
	Pain self-efficacy	Pain Self-Efficacy Questionnaire (PSEQ) [51] (general) and Custom Pain Self-Efficacy Questionnaire with VR as a referent (inside the VR headset and outside the VR headset)	2 in each
	Pain acceptance	Chronic Pain Acceptance Questionnaire (CPAQ) [52]	8
	Pain catastrophizing	Pain Catastrophizing Scale (PCS^d^) [49]	4
	Pain medication	Custom Analgesic Medication Use Survey	3 with branching logic to additional 7
	Health care utilization	Custom health care utilization survey for cLBP^e^	5 at baseline and 6 at all other timepoints
	Other measures		
	Assessment of affect	Positive and Negative Affect Schedule (PANAS) [55]	20
	Susceptibility to virtual reality treatment	Involvement subscale from the Immersive Tendency Questionnaire (ITQ – Involvement subscale) [54]	7
	Acceptability	System Usability Scale (SUS) [53]	10
	Perceived treatment assignment	Perceived Treatment Assignment survey	1

^a^DVPRS: Defense and Veterans Pain Rating Scale.

^b^PROMIS: Physical Function and Sleep Disturbance.

^c^VR: virtual reality.

^d^The 4 questions were selected from the PCS to decrease participant burden.

^e^cLBP: chronic lower back pain.

**Table 2 table2:** Timeline of measures.

Measure	Pre-treatment (days –14 to 0)		Active treatment (days 1-56)		Postintervention (months 1-6 after the end of the study)			
	Baseline assessment (Day –14)	Pain surveys (Days –10, –7, –4, and 0)	Biweekly surveys	End of treatment (day 56)	Follow up 1 month	Follow up 2 months	Follow up 3 months	Follow up 6 months
DVPRS-I^a^ and DVPRS-II	X	X	X	X	X	X	X	X
PGIC^b^				X	X	X	X	X
PROMIS^c^ physical function	X			X	X	X	X	X
PROMIS sleep disturbance	X			X	X	X	X	X
Pain self-efficacy measures	X			X	X	X	X	X
PCS^d^	X			X	X	X	X	X
CPAQ-8^e^	X			X	X	X	X	X
Opioid use	X			X	X	X	X	X
Health care utilization	X			X				
Patient satisfaction					X	X	X	X
Device utilization			X	X				
VR^f^ usage data			X	X				
PANAS^g^	X			X				
SUS^h^				X				
ITQ^i^—involvement subscale	X							
Perceived treatment assignment								X

^a^DVPRS: Defense and Veterans Pain Rating Scale.

^b^PGIC: Patient’s Global Impression of Change.

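### Patient satisfaction has no pre-treatment rating, so the only effect named for it, Intervention × Time, does not test the hypothesised difference between arms

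*Protocol article*

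**What the plan says.** **Status and hypothesis.** The abstract's Methods paragraph includes user satisfaction among the secondary outcomes and adds: "We hypothesize superiority for the skills-based VR program in all of these measures compared to the control condition". Table 1 places the custom "Patient Satisfaction" survey under Secondary Outcomes, on a different row from the PGIC.

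**Timing.** Table 2 marks patient satisfaction at follow-up months 1, 2, 3 and 6 only. Baseline, the pain surveys, the biweekly surveys and day 56 are blank. Additional Custom Surveys describes the instruments as "including one designed to assess satisfaction with each condition", so a rating before treatment could not exist.

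**Analysis.** The third exploratory analysis is the only one that names the survey: "we will assess Intervention × Time effects for DVPRS Pain Rating, opioid drug use, PROMIS physical function, PROMIS sleep disturbance, PSEQ-2, PCS, CPAQ-8, Patient satisfaction". The model is then given: "We will use a 2-factor ANOVA with intervention (EaseVRx vs Sham VR) as an independent groups factor and time as a dependent groups factor". The post hoc t-tests "will be utilized to isolate the locus of any effects". General Approach sets the same target for the mixed models: "The effect of interest will be the time × treatment group effect". It also fixes the error rate: "All analyses will involve 2-sided hypothesis tests, with α=.05".

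**PGIC.** Secondary Analyses says that the PGIC, which also has no baseline, will be compared at end of treatment and at the follow-ups.

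**The concern.** For an outcome measured before treatment, randomization makes the expected gap at baseline zero. A later benefit therefore appears as a change in the gap, and the interaction carries the treatment effect. Satisfaction sits in the same list of nine outcomes without that anchor. Its interaction compares the post-treatment visits only with one another.

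The hypothesis stated in the abstract concerns level: EaseVRx users more satisfied than Sham VR users. The named effect concerns change in that difference between months 1 and 6. If the named effect is taken as the test of the hypothesis, a steady advantage would usually come out as non-significant. A difference in how fast satisfaction fades could come out as significant and be mistaken for a satisfaction benefit.

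**Working it through.** **1. The plan's own figures.** The article gives no power figure for satisfaction. Sample Size Determination gives 45 per group for 90% power on pain intensity, 40% attrition, and 75 to 90 randomized per group. The inflation reproduces: 45 / (1 − 0.40) = 75. The 45 itself cannot be checked, because no SD is given for the difference of 1.48 − 0.756 = 0.724. These figures are used below only for plausible numbers per arm: 45, 75 and 90.

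**2. What the interaction tests.** Let δ(t) be the EaseVRx minus Sham VR mean at month t.

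- Interaction null: δ(1) = δ(2) = δ(3) = δ(6).
- Null that matches the superiority hypothesis: the average of δ(1), δ(2), δ(3), δ(6) is 0 (or δ is 0 at one chosen visit).

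If δ(t) = c at every visit, each deviation from the average is c − c = 0. The interaction null is then true for every c, and a valid test rejects at α = 0.05. With a baseline value, δ(0) = 0 and δ(t) = c afterwards would violate the interaction null. This step needs no assumed input.

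**3. Size.** Simulated two-group × four-visit repeated-measures ANOVA on complete data, 4,000 runs per setting. Assumptions, none of them in the article: a constant gap of 0.5 SD and equal correlation r between visits.

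| Per arm | r | Interaction rejects | Intervention main effect rejects | Bonferroni t-tests by visit, not gated |
|---|---|---|---|---|
| 45 | 0.3 | 4.9% | 92.3% | 79.8% |
| 45 | 0.5 | 5.3% | 84.0% | 74.4% |
| 45 | 0.7 | 4.5% | 75.7% | 67.1% |
| 75 | 0.3 | 4.5% | 99.3% | 96.2% |
| 75 | 0.5 | 4.7% | 97.6% | 93.4% |
| 75 | 0.7 | 5.1% | 93.0% | 88.3% |
| 90 | 0.3 | 4.8% | 99.8% | 98.4% |
| 90 | 0.5 | 4.6% | 98.5% | 96.2% |
| 90 | 0.7 | 5.1% | 96.9% | 94.3% |

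Check of the main effect by formula: the SD of a four-visit mean is √((1 + 3r)/4), and power is Φ(δ / (SD·√(2/n)) − 1.96).

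- n = 45, r = 0.7: SD = √(3.1/4) = 0.880; 0.5 / (0.880 × 0.211) = 2.69; Φ(0.73) = 0.77.
- n = 90, r = 0.3: SD = √(1.9/4) = 0.689; 0.5 / (0.689 × 0.149) = 4.87; Φ(2.91) = 0.998.

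Both agree with the simulation.

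**4. Sensitivity.**

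- Across steady gaps of 0.3, 0.5 and 0.8 SD with equal correlation, the interaction rejected in 4.5% to 5.9% of runs.
- With correlation decaying over months (0.8 per month) and no sphericity correction it rejected in 5.8% to 7.3%; its rate with no gap was then itself about 6%.
- If the t-tests are run only after a significant interaction, they find a steady gap in at most 5.6% of runs (7.0% with decaying correlation).
- For a steady 0.3 SD gap, the main effect rejects in 36% to 53% at 45 per arm, 54% to 76% at 75 and 64% to 83% at 90.

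**The case against.** **The model already contains the right contrast.** A 2-factor ANOVA yields an intervention main effect, and the plural in the post hoc sentence could cover it. General Approach also lists treatment group as an explanatory factor and says that model-predicted values will be reported. This stands in part. A reader might infer that a real acceptability advantage would be reported as no effect. The article does not support that, because the means and the main effect would be at hand. What remains is that both sections name the interaction as the effect assessed, and neither designates the main effect for satisfaction.

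**Satisfaction may mean the PGIC.** The secondary objective uses the word satisfaction for the PGIC, and the abstract's outcome list never names the PGIC. On that reading the hypothesis already has a direct comparison. This narrows the point without removing it: Table 1 lists the custom survey as its own secondary outcome, and the exploratory analysis names it without a direct comparison.

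**The PGIC shares the problem.** A reader might infer this because it too lacks a baseline. The documents do not support it. Secondary Analyses states a comparison at end of treatment and follow-ups, and reserves its repeat-the-above wording for the other outcomes.

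**The interaction serves the exploratory objective.** That objective concerns changes in satisfaction over 6 months, and the interaction does address it. It does not address the superiority hypothesis.

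**The analysis is exploratory, and details may be left to the SAP.** The first half lowers the severity. On the second, nothing is said to be missing: the article names an effect, and that effect does not match its hypothesis for this outcome.

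**Conclusion.** The point holds for patient satisfaction alone. The named effect cannot test the stated hypothesis when the gap between arms is steady. It then rejects at about 5% whatever the size of the gap, and this follows from the measurement schedule without further assumption.

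The contrast with 76% to 99.8% power for the main effect is illustrative. It rests on an assumed, exactly constant 0.5 SD gap, assumed correlations of 0.3 to 0.7, complete data, and a total score that the article does not define (Table 1 gives 8 items plus 15 open-ended questions). It is not a measured power loss for this trial: a gap that grows or shrinks between months 1 and 6 would give the interaction some power.

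Severity is low to moderate. One exploratory analysis of one secondary outcome is affected. The primary pain endpoint, the PGIC comparison and the eight other outcomes in the same list, all of which have a pre-treatment value in Table 2, are not.

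**What to change.** Add one sentence to the third exploratory analysis. For patient satisfaction, which has no pre-treatment value, the effect of interest is the EaseVRx versus Sham VR contrast, either averaged over months 1, 2, 3 and 6 or at one visit named in advance. Intervention × Time is kept as a secondary look at whether that difference changes over follow-up. The choice between the average and the single visit should be made before the groups are unblinded.

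The cost is that sentence. The model stays the same, and no extra data or participants are needed. The PGIC text needs no change on this account.

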### Sample Size Determination

In terms of sample size considerations, a power analysis was performed using data from a recent at-home cLBP study that we conducted. DVPRS pain intensity scores were collected from 39 individuals at baseline, during, and immediately following a 21-day, skills-based VR intervention, and from 35 individuals at baseline, during, and immediately following an audio-only version of the 21-day program. The average difference score was 1.48 for the VR group and was 0.756 for the audio-only group (on an 11-point scale). Assuming an α level of .05 and 90% power, we would need 45 participants per group to observe a treatment × time interaction. In case of high attrition (40%), we will randomize at least 75 participants per group and if possible up to 90 participants per group.

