#### Primary Analyses

The primary endpoint will be the time course of DVPRS-I Pain scale rating at baseline (defined as the average of 3 DVPRS-I Pain Scale ratings obtained during the 2 weeks before enrollment/randomization), at 8 weekly time points (twice per week) across the 8-week intervention, and immediately following the intervention. We will use a linear mixed model as described above.

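### The exploratory analyses credit bootstrapping with handling missing data, but it keeps the attrition bias of whatever estimator it is applied to

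*Protocol article*

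**What the plan says.** The Exploratory Analyses section opens by placing all of its analyses under the linear mixed-model strategy set out earlier. It then names a different method for two of them: a two-factor ANOVA for the third, and a one-factor repeated-measures ANOVA for the fourth. The fourth follows pain skills at six time points (baseline, end of treatment, and 1, 2, 3 and 6 months), "only in the EaseVRx group. We will use a one-factor repeated-measures ANOVA".

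The fourth item closes with a sentence that begins "When appropriate, we will also utilize more robust statistical approaches" and describes these as "more robust statistical approaches that better address missing data and do not assume distributional normality, such as bootstrapping". This is the only mention of bootstrapping in the article.

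Elsewhere the plan is different. Under General Approach, "The data will be analyzed in a mixed-model framework (PROC GLIMMIX in SAS) with 3 explanatory factors", and "The analytic method used will not involve imputing missing data for estimating the significance of the effects specified in the model". Under Primary Analyses, "We will use a linear mixed model as described above".

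**The concern.** The sentence gives bootstrapping two properties: that it copes better with missing data, and that it does not need normality. Only the second is true. The bootstrap estimates the sampling variability of an estimator by resampling the data at hand. If the estimator is off-centre because the participants who stayed differ from those who left, each resample is drawn from the same selected data and is off-centre by the same amount.

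This matters for the fourth analysis because a conventional repeated-measures ANOVA drops any participant with a missed visit, and here there are six visits over more than six months. The sentence concedes that missing data may need something better than the ANOVA, and then names a tool that does not supply it. A bootstrapped ANOVA result could be reported as robust to attrition when it is robust only to non-normality.

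**Working it through.** **1. The plan's own attrition figure.** Sample Size Determination needs 45 per group and allows for 40% attrition: 45 / (1 − 0.40) = 75 per group, which reproduces the stated minimum. That figure is not in dispute. It shows only that attrition of this order was considered possible.

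**2. What bootstrapping can and cannot change.** For completer changes d₁, …, dₘ the estimate is their mean. A bootstrap resample draws m values from the same list, so the expected bootstrap mean equals the completer mean. Any gap between the completer mean and the mean of everyone randomized stays in place. This does not depend on the numbers chosen below.

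**3. Illustration of size.** The article gives no scale or standard deviation for the pain-skills items, so all of these inputs are assumptions, apart from 90 and 40%, which are borrowed from Sample Size Determination.

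- One arm, n = 90 (the upper recruitment target per group), three visits, last visit missing for about 40%.
- Baseline y₀ = b + e₀; second visit y₁ = 1 + b + c + e₁; last visit y₂ = 1 + b + c + e₂. Here b, c and each e are independent normal with SD 0.7.
- The true mean change from baseline to the last visit is 1.00. The SD of that change is √(3 × 0.49) = 1.21.
- Probability of being observed at the last visit: 0.6 for everyone (missing completely at random, MCAR); logit = 0.5 + 1.2(y₁ − 1) (missing at random, MAR); logit = 0.5 + 1.2(y₂ − 1) (missing not at random, MNAR).
- 1000 replicates, with 200 bootstrap resamples for the completer interval and 40 for the all-data estimate.
- The all-data estimate regresses y₂ on y₀ and y₁ in completers, predicts for all 90, averages, and subtracts the mean of y₀. With this dropout pattern it is the maximum-likelihood estimate for a normal model with a separate mean at each visit and an unstructured covariance.

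| Mechanism | Observed | Completer mean | Bootstrapped completer mean | Coverage of 95% bootstrap interval | All-data estimate | Bootstrap of all-data estimate |
|---|---|---|---|---|---|---|
| MCAR | 60.1% | 1.001 | 1.001 | 92.5% | 0.997 | 0.995 |
| MAR | 59.1% | 1.172 | 1.172 | 79.8% | 0.999 | 0.999 |
| MNAR | 58.5% | 1.349 | 1.349 | 37.0% | 1.314 | 1.313 |

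**4. Reading the table.**

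- Under every mechanism the bootstrap mean is within 0.002 of the estimator it wraps.
- Under MAR the completer bias is 1.172 − 1.00 = 0.172. The all-data estimate removes it (0.999).
- Under MNAR the completer bias is 0.349, and the all-data estimate removes 1.349 − 1.314 = 0.035, about one tenth of it.
- Under MCAR there is no bias to carry over. The 92.5% coverage there shows that a small part of the shortfall in the other rows is not due to attrition.

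**The case against.** The strongest reply is that this is one loose phrase in a minor place. The sentence is conditional and additional, it speaks of approaches in the plural with two aims, and bootstrapping does serve one of them. The article never says that completer means will be resampled. Wrapped around a model that is valid under MAR, the bootstrap keeps that validity (0.999 above). A condensed article may also leave to the full plan what is resampled. All of this stands, and it limits the point to a wrong attribution in one exploratory analysis. It does not make the attribution right: the only method linked to missing data in that sentence lacks the property, and the estimator named just before it is an ANOVA.

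Three stronger readings are tempting, and the document does not support them.

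- *That the trial's remedy for missing data does nothing.* The primary analysis, and the secondary analyses that repeat it, use a mixed model on the observed repeated measures and do not rely on bootstrapping.
- *That bootstrapping is the only remedy because imputation is ruled out.* The sentence on imputation describes how effects in the mixed model are tested; it is not a general ban. The exploratory section also starts from the mixed-model strategy.
- *That the low coverage under MNAR is the cost of this sentence.* Most of that loss would remain under any standard MAR-based method.

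Nor does the article say that the bootstrap sentence covers the third analysis; it closes the fourth.

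**Conclusion.** The point holds as a minor error of method and wording. The article wrongly says that bootstrapping helps with missing data in the fourth exploratory analysis, which is a single-arm analysis with no treatment comparison. The same section also contradicts itself by announcing mixed models for all exploratory analyses and then naming ANOVA for the third and fourth. No primary or secondary conclusion is at risk.

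That the bootstrap keeps the bias of its estimator is general. The size is illustrative: under the assumed inputs, about 0.17 on a true change of 1.00 with roughly 80% coverage under MAR. It also assumes that the ANOVA is run on completers, which is conventional but not stated.

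**What to change.** Revise the Exploratory Analyses section as follows.

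- For the third and fourth analyses, replace ANOVA with the likelihood mixed model of General Approach, fitted to all available visits. In the single-arm fourth analysis the model has time as its only factor. If ANOVA is kept, use multiple imputation with it.
- Describe bootstrapping as a remedy for non-normality only. Where it is used, resample whole participants, including those with missed visits, and refit the same mixed model in each resample.
- Do not present the change as a cure for informative dropout. It removes bias when missingness depends on observed values and the model is correctly specified; in the MNAR case above it moves the estimate only from 1.35 to 1.31.

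The cost is a few sentences and standard software. Design, sample size and data collection do not change, and the edit also settles the section's conflict between mixed model and ANOVA.
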